### ***The intervention group***

#### ***Online promotion of HIVST-Chatbot***

Participants in the intervention group will watch an online video promoting HIV testing in general and HIVST-Chatbot. The first part of the online video promoting HIV testing generally is the same as the one for the control group. In the second part, the same MSM narratively discusses the advantages of HIVST-Chatbot (no need to wait for an appointment, operates 24 hours a day, artificial intelligence) and the availability of real-time support from Chatbot and supporting staff (if users receive positive screening results). The video will also demonstrate the procedures of the HIVST-Chatbot. Project staff will help the participants connect to the Chatbot. Participants are guaranteed anonymity during the implementation.

#### ***Signing up for HIVST-Chatbot***

Participants will receive a free HIVST kit in the same manner. The Chatbot will contact the participants to confirm receipt of the kits. Participants can get the Chatbot to implement HIVST without a prior appointment.

#### ***Implementation of HIVST-Chatbot***

##### ***1) Pre-test counseling***

When users contact the Chatbot for implementation, the Chatbot will provide standard-of-care pre-test and post-test counseling covering key components listed in the Quality Assurance Guideline on HIV Testing and Counseling Services in the format of text messages or videos. The workflow of the HIVST-Chatbot is presented in Figure 2.

[figure not shown]

**Figure 2. The workflow of the HIVST-Chatbot**

a) Risk assessment: The Chatbot will ask some standard questions to assess users' HIV risk (e.g., injective drug use, use of condoms and alcohol/drug during sexual behaviors, and use of pre-exposure prophylaxis) and show the response categories. After users complete the questions, the Chatbot will interpret their responses and define their risk level. The questions and definition of risk level are identical to those used by facility-based HIV testing and counseling services in Hong Kong (multimedia appendix 1).

b) Providing health education advice tailored to risk level: The Chatbot will inform users about their risk level and explain the rationale. For high-risk users, the Chatbot will prepare them for potential positive results. It will explain the implication of positive screening results and follow-up procedures and emphasize that the staff of collaborative CBO will provide immediate support for users receiving positive testing results from 10:00 am to 9:00 pm (Monday to Friday). These users are advised to perform HIVST within such a timeframe. For users without high risk, advice on maintaining safe sex practices is provided. Users can skip parts a) and b). If they prefer to skip these parts, standard pre-test information will be sent to them (e.g., window period of HIVST, types of sexual behaviors with a high risk of HIV transmission).

c) Addressing concerns and obtaining consent for HIVST. Users can choose one or more references from a list of common concerns identified by literature review and interviews of local MSM and service providers. In case their problems are not included in the list, the participant can raise them verbally or in written text. The Chatbot will interpret users' input, extract keywords, retrieve relevant information from the knowledge graph, and prepare a response in the text to the participants. Ultimately, the Chatbot will ask whether users are ready to perform HIVST.

## 2) Instruction on how to use the HIVST kit

The Chatbot will play a pre-recorded online demonstration video showing the procedures of using an oral fluid-based/blood-based HIVST kit. Users can watch the demonstration video repeatedly. They can also skip it if they are familiar with the procedures.

### 3) Reporting testing results

The Chatbot will show examples of positive, negative, and invalid results to help the users interpret them. Users will report their results by answering a multiple-choice question.

The Chatbot will ask the users to take a photo of their testing result and upload it to a secure webpage for verification.

### 4) Post-test counseling

For users receiving negative testing results, the Chatbot will explain that the user is not infected unless the test was taken within the window period, remind them about the risk of HIV infection, and provide advice for safe sex practices. Ultimately, the Chatbot will emphasize the need for regular HIV testing.

For users receiving positive testing results, the Chatbot will automatically notify a designated supporting staff from the collaborative CBO after obtaining users' consent. The supporting staff will follow up with the user as soon as possible. The Chatbot will explain: a) this is a preliminary positive test result, b) further confirmatory testing in the Department of Health is required, c) a staff from collaborative CBO is already notified and will follow up with them as soon as possible, and d) emphasize that HIV treatment is very effective. Hotline numbers for 24-hour emotional support and the collaborative CBO will also be provided. Our project staff may accompany them to visit the collaborative CBO or the Department of Health if desired.

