### **The control group**

#### ***Online promotion of HIVST-OIC***

Participants will watch a 7-minute online video promoting HIV testing in general and HIVST-OIC developed by previous projects. The online video is based on the constructs of perceived benefits and perceived barriers of the Health Belief Model. The video has two parts. The first part is to promote HIV testing in general. A local MSM introduces the potential benefits of taking up HIV testing in general (e.g., help to detect HIV infection earlier, increase trust between sex partners and reduce psychological burdens) and the WHO recommendation for MSM with risk behaviors to take up HIV testing every six months. In the second part, the same MSM narratively discusses the benefits and barriers of HIVST-OIC, demonstrates its procedures, and emphasizes the availability of real-time online support.

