### ***Signing up for HIVST-OIC***

After completing watching the online video, participants are asked to select their preferable HIVST kits (oral fluid-based or blood-based), choose a service model (comprehensive version with real-time instruction, pre-test, and post-test counseling, or simplified version with real-time post-test counseling only), and fill in their contact information and address to receive the HIVST kits. Participants can receive a free HIVST kit through rapid courier service, mail it in a plain envelope, or pick it up at collaborative CBO or the research office. Participants can make an appointment with trained HIV testing administrators to implement HIVST-OIC after receiving the HIVST kit. OraQuick® in-home test kit (OraSure Technologies, Inc.; sensitivity: 91.7%; specificity: 99.9%) and BioSure® HIV self-test kit (BioSure, Inc.; sensitivity: 99.7%; specificity: 99.9%) will be used in this study.

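### The Chatbot's message after a negative result excludes infection outside the window period, which the stated kit sensitivities (91.7% and 99.7%) do not support

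*Protocol*

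**What the plan says.** The content for negative results is set out once, under 4) Post-test counseling: "the Chatbot will explain that the user is not infected unless the test was taken within the window period". The Chatbot then reminds the user of HIV risk, gives safer-sex advice and stresses regular testing. For positive results the same section lists "a) this is a preliminary positive test result, b) further confirmatory testing in the Department of Health is required".

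Kit performance is given under Signing up for HIVST-OIC: "OraSure Technologies, Inc.; sensitivity: 91.7%; specificity: 99.9" for the oral-fluid kit and "BioSure, Inc.; sensitivity: 99.7%; specificity: 99.9" for the blood kit (all percentages). Both reach the Chatbot arm. Under Signing up for HIVST-Chatbot, "Participants will receive a free HIVST kit in the same manner", and the instruction video is described as "showing the procedures of using an oral fluid-based/blood-based HIVST kit".

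More generally, the Chatbot's counseling is described under 1) Pre-test counseling as "covering key components listed in the Quality Assurance Guideline on HIV Testing and Counseling Services". That guideline is cited but not reproduced.

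**The concern.** A test that misses some infected users cannot, when negative, establish that the user is uninfected. The Protocol's sentence allows one reason for a wrong negative, testing too early, and no other section adds a second. A man with a false negative and no recent exposure would conclude from the message that he is free of HIV.

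The likely harm is delay until his next test, with possible onward transmission meanwhile. The wording carries some weight because, under Online promotion of HIVST-Chatbot, staff support is described for positive results. For most men who test negative, the automated message is therefore the whole of the post-test counseling.

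**Working it through.** The Protocol gives no figure for residual risk after a negative result, so there is none to reproduce. The arm size used below does reproduce: 198 per group for a 10% margin at 80% uptake, one-sided 0.05 and 80% power, then 198 / 0.75 = 264.

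**Inputs from the Protocol**
- Oral kit: sensitivity (Se) 0.917, specificity (Sp) 0.999. Blood kit: Se 0.997, Sp 0.999.
- Arm size 264. Uptake 80%, which is the control-arm assumption under Sample size planning.
- HIV prevalence in local MSM 6.54% (Background). Diagnosed men are excluded (Participants and recruitments), so for undiagnosed infection I treat this as an upper bound.

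**Assumptions**
- Undiagnosed prevalence p of 1%, 2% or 6.54%. The Protocol gives no value.
- Chatbot-arm uptake of 80%, with every tester using the Chatbot.
- Kit mix unknown, so all-oral, half-and-half and all-blood are shown.

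**Step 1. Testers and infected testers.** 264 × 0.80 = 211.2 testers. Infected = 211.2 × p = 2.11, 4.22 and 13.81.

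**Step 2. Expected false negatives** = infected × (1 − Se).

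| Kit mix | Miss rate | p = 1% | p = 2% | p = 6.54% |
|---|---|---|---|---|
| All oral | 0.083 | 0.18 | 0.35 | 1.15 |
| Half and half | 0.043 | 0.09 | 0.18 | 0.59 |
| All blood | 0.003 | 0.006 | 0.013 | 0.041 |

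If all 264 men tested with the oral kit, the range would be 264 × p × 0.083 = 0.22 to 1.43.

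**Step 3. Probability of infection after a negative result** = p(1 − Se) / [p(1 − Se) + (1 − p)Sp].
- Oral, p = 6.54%: 0.0054282 / (0.0054282 + 0.9336654) = 0.00578, about 1 in 173.
- Oral, p = 1%: 0.00083 / (0.00083 + 0.98901) = 0.00084, about 1 in 1,193.
- Blood: 0.00021 at 6.54% and 0.00003 at 1%.

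**Step 4. Window-period share.** The Protocol does not say whether its sensitivities include window-period infections, for which the message already has an exception. If half of the oral misses are of that kind, the all-oral counts outside the window are 0.09, 0.18 and 0.57. If all of them are, the count is 0 and the sentence is correct.

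**Step 5. Comparison with positives.** Expected false positives = 211.2 × (1 − p) × 0.001, about 0.2. With the oral kit, the predictive value of a positive is 1.937 / (1.937 + 0.209) = 90.3% at p = 1% and 98.5% at 6.54%. A single negative is therefore more certain than a single positive.

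**The case against.** The section summarises content and is not the delivered script. The guideline it relies on cannot be seen, so the actual message may say more. The only miss rate that contradicts the sentence is the one outside the window, and that rate is unknown. Negatives already carry one caveat, and much mitigation is in place: advice on risk and regular testing, "the WHO recommendation for MSM with risk behaviors to take up HIV testing every six months" in the video part shared by both arms, and a photograph of the result uploaded for verification.

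Most of this stands and keeps the point small. It does not remove it. The content as stated is itself too firm, and nothing in the Protocol shows that misses outside the window are zero. The Background also raises concern about incorrect self-test procedures, and the demonstration video may be skipped. A photograph can catch a misread strip but not a poor sample or a true kit miss.

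A reader might infer three stronger things that the documents do not support:
- That 8.3% of oral-kit negatives are wrong. The 8.3% applies to infected users. Among negatives the share is at most about 0.58% under the assumptions above.
- That because positives are called preliminary, negatives need equal caution or confirmatory testing. Step 5 shows the opposite ordering of certainty, so more caution for positives is proportionate.
- That the control arm shares the fault, or that the arms differ in this respect. Implementation of HIVST-OIC gives no content for negative results, so neither can be claimed.

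**Conclusion.** The stated message overstates what a negative self-test shows, judged against the Protocol's own kit figures. It is a low-priority participant-safety point, worth correcting because the correction is small. Expected false negatives are about 0.2 to 1.1 men if all testers use the oral kit, and fewer with any use of the blood kit or if some misses fall in the window period. These figures rest on the assumed prevalence range, kit mix, 80% uptake and use of the Chatbot by every tester.

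The primary outcomes concern having tested and having received counseling, and the message comes after the test. Nothing in the Protocol links the wording to the outcomes, the analysis or the sample size. Confidence is moderate, because the delivered text and the miss rate outside the window are both unknown.

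**What to change.** Revise the negative-result content under 4) Post-test counseling so that the Chatbot says:
- a negative self-test makes HIV infection unlikely but does not rule it out;
- the test can miss infections, especially in the window period, and more often with the oral-fluid kit than with the blood kit;
- users with a recent risk or symptoms should repeat the test, and everyone should test regularly.

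Separately, check that the control-arm administrators' existing counseling for negative results is consistent with this. Change it only if it makes the same overstatement, since the comparator is meant to follow its established procedures.

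The cost is one content line in the Chatbot, a short amendment and the control-arm check. The downside is slightly less reassurance and possibly a few more tests elsewhere. Those tests count toward the secondary outcome of other HIV testing, and the added advice may not be taken up equally in the two arms.

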## Development of the HIVST-Chatbot

### *The architecture of the Chatbot system*

We adopted the WhatsApp platform to implement the Chatbot. The Chatbot is integrated with WhatsApp through its public Web API services. Participants' messages are sent to WhatsApp's instant messaging server and a separately constructed Chatbot system (an administrative system and the Chatbot). The Chatbot system processes and sends a message back to the WhatsApp instant messaging server. Finally, the users can view the message sent by the Chatbot. The entire process spans less than a second without a sluggish feel for users.

The Chatbot system contains three modules.

1) Dialogue management module: The dialogue system records all conversations between users and the Chatbot. The system can extract context information such as basic statistics of users' activities and prior interaction between a user and the Chatbot. The natural language processing module analyzes the text content of each message. Then, the message is forwarded to trigger specific actions based on preprogrammed rules. For example, when a user sends a message containing a specific keyword, the Chatbot immediately responds with information that corresponds to that keyword. In addition, the module initiates new conversations based on the preprogrammed intervention plan.

2) User management module: This module records detailed information about user conversations. Administrators can link users' WhatsApp numbers with the Chatbot and review the progress of the intervention delivery (e.g., number of completed sessions, disconnection between users and the Chatbot).

3) Multi-media management module: The Chatbot system supports image uploading, sending, and updating through this module to allow image and video exchange.

### *Preparation of knowledge graph*

To build a system that addresses various personal and relevant concerns related to HIV, HIV testing, and HIVST, we created a knowledge graph linking questions and responses. We conducted in-depth interviews with 10 local MSM to crowdsource concerns related to HIV, HIV testing, and HIVST. We also interviewed experienced HIV testing administrators, CBO workers, and experts in HIV prevention to obtain responses addressing these concerns. The knowledge graph will be used to set rules for the Chatbot and train it to get familiar with and identify commonly encountered concerns/misinformation and how to address them through machine learning.

The knowledge graph will evolve over time with more prior interactions during the intervention period.

### ***Conversation mechanism***

1) The Chatbot uses a mixture of techniques so that a dialogue is not merely rule-based, but it can also learn from a big pool of prior conversation patterns through machine learning. The Chatbot resolves the recent conversation to create a plan for a suitable response. Relevant information is retrieved and used for the preparation of a reply. A persuasion template is selected in accordance with the current stance of the conversation and the perceived user characteristics by the Chatbot. The pool of prior conversation patterns will grow bigger after extended usage, and the variety of responses will increase accordingly.

2) In case there is no relevant response to participants' input, the Chatbot will respond by saying, "I am not confident about an answer to your question." The Chatbot will suggest a new conversation topic after three off-topic inputs from the user.

3) In case the participants want to know more about one topic. The Chatbot will respond differently within the knowledge graph to the same topic. Upon request, the Chatbot can also repeat the response.

4) In case the conversation between Chatbot and the participants is interrupted. The Chatbot will cancel participants' incomplete input and invite them to input again.

5) The Chatbot will document prior conversations with the users and avoid responding repetitively to users' questions.

### ***Pilot testing and refinement***

We purposely recruited 30 MSM who were HIV negative or unknown sero-status to use the HIVST-Chatbot. With informed consent, the research team retrieved and reviewed users' interactions with the Chatbot. Feedback was also collected from these users. The pilot study showed that the Chatbot was running smoothly. Users were satisfied with the performance and interface of the Chatbot.

### ***Measurements***

#### ***Primary outcomes***

The primary outcomes of this study are self-reported uptake of any HIVST at Month 6 and the proportion of HIVST users self-reported having received counseling along with HIVST during the follow-up period. The Chatbot will accurately document the number of HIVST-Chatbot use, while HIV testing administrators will record the number of HIVST-OIC performed.

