## Methods

### Study design

A parallel-group non-inferiority randomized controlled trial will be conducted. A total of 528 participants are randomized 1:1 to either the intervention group (n=264) or the control group (n=264). We will promote and implement HIVST-Chatbot and HIVST-OIC in the intervention group and control group, respectively. A telephone follow-up evaluation will be conducted six months after the baseline survey by blinded interviewers. The study was registered at ClinicalTrial.gov (number NCT05796622). A flowchart diagram is shown in Figure 1.

[figure not shown]

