## Statistical analysis

Intention-to-treat analysis will be performed. Multiple imputations will handle missing values at Month 6. Markov Chain Monte Carlo method will be used to impute data with the arbitrary pattern of missing values, while monotone methods are used to impute data having a monotone pattern of missing values. Predictors included baseline background characteristics and baseline values of these outcomes. The relative risk reduction, absolute risk reduction, and number needed to treat, and their 95% confidence interval will be calculated using Excel. The chi-square tests will inspect between-group balances of potential confounders at baseline. Adjustments will be made if any potential confounders show  $P < .05$  in the comparisons. SPSS 26.0 for Windows (SPSS Inc., Chicago, IL) will be used for all analyses; statistical significance is set at the  $P < .05$  level (one-sided).

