## Discussion

The COVID-19 pandemic and its control measures (e.g., lockdown, closure of business, physical distancing) have direct and negative impacts on HIV testing service utilization among MSM, especially for facility-based HIV testing services. Across countries, health authorities have been actively promoting HIVST to mitigate such negative impacts. As a result, there was an increase in HIVST use among MSM. Such growth may continue even in the post-pandemic era. Therefore, ensuring sufficient support and linkage to care for the increasing number of MSM HIVST users becomes more important. Although evidence-based HIVST services existed (e.g., HIVST-OIC), most required intensive resources to implement and maintain. Such constraints limited their public health impacts. To our knowledge, this is the first attempt to apply an artificial intelligence Chatbot to deliver real-time instruction and counseling support to HIVST users. This RCT will compare the efficacy of the HIVST-Chatbot with an evidence-based HIVST service, the HIVST-OIC, in increasing HIVST uptake and the proportion of HIVST users receiving counseling along with the testing. If HIVST-Chatbot is proven non-inferior to HIVST-OIC in improving HIVST uptake and coverage of counseling among users, it may address the existing HIVST service gaps. Since HIVST-Chatbot is fully-automated and requires fewer resources to implement and maintain, it can be promoted and implemented by governmental organizations and CBOs in Hong Kong as an alternative approach to HIVST-OIC. The HIVST-Chatbot has the potential to overcome the barriers to using HIVST (e.g., concerns about lack of support and missing linkage to care), improve overall HIV testing coverage, and reduce the HIV burden among MSM.

Although the trial will yield essential insights for HIVST program planning and policymaking, it has some limitations. First, the use of HIV testing other than HIVST-Chatbot or HIVST-OIC is self-reported. Such responses may be over-reported due to social desirability. Second, similar to most interventional studies, participants will be recruited through convenient sampling. Caution should be taken when generalizing the findings to MSM in Hong Kong. Third, collecting characteristics of MSM who refuse to participate in the study is difficult. Selection bias may exist.

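### Both primary outcomes are telephone self-report, so as written a self-test that the trial itself recorded would be imputed for any man who misses the Month 6 call

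*Protocol*

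**What the plan says.** The protocol's Primary outcomes section defines uptake by self-report: "The primary outcomes of this study are self-reported uptake of any HIVST at Month 6". It defines the second primary outcome the same way: "the proportion of HIVST users self-reported having received counseling along with HIVST during the follow-up period". Study design gives the mode of collection: "A telephone follow-up evaluation will be conducted six months after the baseline survey by blinded interviewers".

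The next sentence of Primary outcomes describes another source: "The Chatbot will accurately document the number of HIVST-Chatbot use, while HIV testing administrators will record the number of HIVST-OIC performed". It does not say what these records are for. In the Chatbot arm, users choose their result from a multiple-choice question and are asked to "take a photo of their testing result and upload it to a secure webpage for verification". The section on Chatbot architecture says that users' WhatsApp numbers can be linked to the Chatbot's records. In the control arm, an administrator guides the test on-screen in real time (Implementation of HIVST-OIC).

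Statistical analysis says: "Multiple imputations will handle missing values at Month 6". The predictors it lists are baseline characteristics and baseline values of the outcomes. Neither treatment arm nor service records are listed.

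The first limitation in the Discussion is that "the use of HIV testing other than HIVST-Chatbot or HIVST-OIC is self-reported", with a warning that such answers may be over-reported.

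**The concern.** Two things do not fit together. Primary outcomes makes all uptake self-reported, while the Discussion confines the self-report weakness to testing outside the two services, as if service use came from records. Both statements are in the protocol, and they lead to different data for the primary analysis.

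If Primary outcomes is followed, outcomes are missing exactly when the telephone interview is missing. The service records do not depend on that interview. A man whose supported test was logged, and who then drops out, would have his uptake drawn from a model of baseline variables although the trial already knows the answer.

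Self-report also matters more here than in a superiority trial. If non-testers in both arms claim a test at similar rates, the arms look more alike, and in a non-inferiority comparison that makes a false positive conclusion more likely.

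**Working it through.** **The plan's own figure.** Inputs from Sample size planning: uptake 80% (taken as equal in both arms for the calculation), margin 10 points, one-sided 5%, power 80%, dropout 25%.

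- n = (1.645 + 0.842)² × (0.80 × 0.20 + 0.80 × 0.20) / 0.10² = 198 per arm
- 198 / 0.75 = 264 per arm, 528 in total

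This reproduces the protocol and is not in dispute.

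**Recorded events that would be imputed.** Planned dropouts are 264 − 198 = 66 per arm. The protocol gives no testing rate for dropouts. Assume that they test through the assigned service at between half the planning rate and the full rate:

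- 40%: 66 × 0.40 = 26 per arm (10% of the 264 randomised)
- 80%: 66 × 0.80 = 53 per arm (20% of the 264 randomised)

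**Why record status must be in the imputation model.** Suppose recorded tests are set to yes, and the remaining dropouts are imputed at an overall rate of 80%:

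- 40% recorded: 26.4 + 0.80 × 39.6 = 58.1 of 66, or 88%
- 80% recorded: 52.8 + 0.80 × 13.2 = 63.4 of 66, or 96%

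Uptake among dropouts is then pushed above the overall rate. Men without a record have to be imputed from interviewed men without a record.

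**Over-reporting.** Let f be the share of non-testers who claim a test, with no under-reporting. Observed uptake is p + f(1 − p). Take the true rates at the margin, 80% control and 70% Chatbot, with 198 per arm. The chance of declaring non-inferiority is Φ((0.10 − observed gap)/SE − 1.645), where SE is the unpooled standard error. The protocol gives no value of f, so all values below are assumptions.

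| f control | f Chatbot | Observed rates | Gap | False non-inferiority |
|---|---|---|---|---|
| 0 | 0 | 80% v 70% | 10 points | 5.0% |
| 10% | 10% | 82% v 73% | 9 points | 8.0% |
| 20% | 20% | 84% v 76% | 8 points | 12.6% |
| 30% | 30% | 86% v 79% | 7 points | 19.6% |
| 10% | 20% | 82% v 76% | 6 points | 25.3% |
| 20% | 10% | 84% v 73% | 11 points | 2.9% |

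For the 20% row: SE = √((0.84 × 0.16 + 0.76 × 0.24)/198) = 0.040, and Φ(0.02/0.040 − 1.645) = 0.126.

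The observed gap equals the true gap when 0.20 × f(control) = 0.30 × f(Chatbot). The direction therefore reverses once control over-reporting exceeds 1.5 times that in the Chatbot arm.

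**The case against.** The strongest reply is that the protocol never says the records are ignored. The sentence about them stands under Primary outcomes, and the Discussion reads as though they count. A rule for merging records with interview answers could be in a statistical analysis plan that is not at hand. This stands in part: the authors may intend to use the records. But the outcome definition, the list of imputation predictors and the conflicting limitation are all in the protocol, and the definition as written leads to the loss.

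A reader might go further and infer that the primary outcome should be taken from records alone. The documents do not support that:

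- It would change the question, because the chosen outcome is uptake of any HIVST and a man without a record may have tested with another kit.
- It would empty the second primary outcome. Both HIVST-OIC versions include post-test counseling and the Chatbot session is built around counseling, so nearly every recorded user would be counseled by construction.
- The records differ in kind: an administrator watching on-screen in one arm, a self-entered result with a requested photo in the other.
- The apparent power gain is fragile. With 264 outcomes per arm, power is 89% at 80% uptake. If recorded uptake were 70% in both arms (assumption), it is Φ(0.10/√(0.42/264) − 1.645) = 81%.

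A reader might also infer that self-report is bound to favour non-inferiority. The last row of the table shows otherwise. Men know their arm, and greater social desirability among those who dealt with a person is plausible. The Discussion's own warning concerns tests outside the two services; extending it to service use is inference, although any HIVST does include those outside tests.

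**Conclusion.** The point holds in a limited form. Primary outcomes and the Discussion disagree on whether service use is self-reported. Followed as written, the plan discards recorded tests of men who miss the call and imputes them: about 26 to 53 of 66 planned dropouts per arm, if dropouts test at 40% to 80% through the assigned service.

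Over-reporting is a conditional risk. Equal rates of 10%, 20% or 30% among non-testers would raise the error at the margin from 5% to about 8%, 13% or 20%. With 20% in control and 10% in the Chatbot arm it falls to 2.9%.

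Two further inferences are not supported. One is that imputation itself favours non-inferiority. With arm in the model and data missing at random it mainly loses information, and the protocol does not state that arm is left out. The other is that asking about the past six months, as the Abstract does, loses early tests. That would matter only if calls ran late, and no section says they will. Counting kits from any source is a legitimate choice of outcome, not an error.

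**What to change.** 1. Reconcile Primary outcomes with the Discussion, so that both say which source determines uptake through the two services.
2. Keep uptake of any HIVST as the primary outcome, but score it yes wherever a service record exists between randomisation and Month 6, whether or not the man is interviewed.
3. Impute only men with neither a record nor an interview, with treatment arm and service-record status in the imputation model.
4. State how counseling is scored for a man whose uptake comes from a record without an interview, since he enters the denominator of the second primary outcome.
5. Report record-confirmed uptake in both arms as a sensitivity analysis for over-reporting.

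The cost is a few sentences and a small data merge. Linkage to the individual is described for the Chatbot only, so administrators' records must be kept per participant and not just as a count. The protocol should also say that the two kinds of record are not equivalent: administrator-observed in control, user-reported with a requested photo in the Chatbot arm.
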